### Electromyography (EMG)

The placement of the EMG electrodes and preparation of the skin will follow the SENIAM recommendations (http://www.seniam.org). EMG signals will be recorded using bipolar EMG configuration (Blue Sensor N-00-S/25, Ambu A/S, Ballerup, Denmark) with an inter-electrode distance of 2 cm [51], bilaterally from the upper trapezius, placed at 50 % on the line from the acromion and the C7 vertebra, and from the erector spinae, placed at 2 finger width lateral from the spinous process of L1 (http://www.seniam.org). To secure an optimal EMG signal and to lower the skin-impedance the skin of the subject will be preparing with scrubbing gel (Acqua gel, Meditec, Parma, Italy) before mounting of the electrodes. The electrodes and the cables for the EMG will be fixed with tape (Fixomull stretch). The EMG signals will be normalized to maximal voluntary contractions (MVC’s) for the back and shoulders, which will be performed in a standardized procedure at the beginning and end of the working day.

As a supplement to the MVC’s, we will perform standardized reference lifts at the beginning and end of the working day. These reference lifts will be performed by lifting a weight of 30 kg (lifting limit for Danish workers) from the floor to a table five times in a standardized manner with a 10 s break between each lift.

### Awkward postures and kinematics

The kinematics of the back and shoulder will be measured using accelerometers. The accelerometers will be mounted on the upper back at the level of T1-T2 [52], lower back [53], bilateral on the upper arms below the insertion of the deltoid muscle [52], on the thigh [53] and the shank. The data will be processed in line with previous studies [30, 52].

### Video

Portable video cameras (Reveal Media, UK) will be placed on the chest of workers using a harness, thereby allowing for continuous recording during the working day. This will enable the identification of work tasks with excessive load.

### Data

EMG, kinematics and video data will be collected simultaneously to identify episodes with excessive load. The method is considered cost efficient since the researcher will not have to view 7-8 h of video manually, but only the sequences with measurements of excessive physical load (see below).

Reference lifts of 30 kg will be performed in the morning and in the afternoon, and will be used to normalize the working day EMG. Events will be defined as normalized EMG amplitudes that exceed the maximal EMG amplitude obtained during the reference lifts (averaged for morning and afternoon).

The sequences with excessive physical load will be calculated based on laboratory recordings investigating EMG activity in standardized lifting situations. The EMG activity will be calculated and used to define the cut points for excessive physical load. However, because the method is new the exact definitions of excessive physical workload will be determined during a pilot study.

Events that fulfill the criteria of excessive load will be extracted for further inspection, and an assessment of the relevance of these events will be made from the following; (i) frequency and duration (ii) physical load and (iii) practical possibility for implementation in the working context. The latter will be assessed at a workshop by the workers and managers based on the video recordings.

The workers will fill out a validated questionnaire at baseline and after the intervention period addressing psychosocial and organizational conditions at the work site [22, 54]. Answers from the baseline questionnaires will be included in the workshop interventions to increase the possibility of making practical changes in the working environment.

### Effect evaluation

The first measurement with technical measurements will serve as baseline and the follow-up measurements will be performed one week after the last workshop to measure short term effect of the intervention. Because there is approximately a month between each workshop the first follow-up measurements will correspond to a 3-month follow-up after baseline. Furthermore technical measurements will be repeated three months after the last workshop to measure the long term effect, i.e. approximately 6 months follow-up after baseline.

### Statistics

Statistical analyses will be performed using the SAS statistical software (SAS Institute, Cary, NC). The change in frequency and duration of events with excessive physical workload will be evaluated using a repeated-measures linear mixed model with *group*, *time* and *group by time* as independent variables. Participants nested within gangs will be entered as random effect to account for clustering. Analyses will be adjusted for baseline values of the number of events with excessive physical workload, gender and age. All statistical analyses will be performed in accordance with the intention-to-treat principle, i.e. including all available data in the analyses regarding actual participation or dropout. If participants do not show up for the intervention they will still be offered participation in the follow-up measurements. A P-value below 0.05 will be accepted as statistically significant. Outcomes will be reported as between-group least mean square differences with 95 % confidence intervals at follow-up.

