### Outcomes

The primary outcome of the present study is the change from baseline to follow-up in frequency of events with excessive physical load. Secondary outcomes are those obtained from the questionnaires, including psychosocial and organizational conditions based on the musculoskeletal pain intensity during the last week (scale 0-10), work ability index, self-efficacy and social capital (within gangs, between gangs and between gangs and their leader).

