### Sample size

Concerning outcome measurements, we expect EMG to be the method with lowest reliability [50]. Consequently, the power calculation is based on EMG. The primary outcome of the present study is the change from baseline to follow-up in frequency of events with excessive physical load. As the methods are new in the way that they are used simultaneously, we do not have any information on the reliability of the primary outcome, and have thus based the power calculations on closely related data. The power calculation shows that to demonstrate a reduction in 20 % in normalized EMG (nEMG) with a SD of ≈20 % in normalized EMG between individuals (based on previous research with EMG during a full working day [29]), and a type I risk of 5 % and a power on 80 % the sample size should have a minimum of 17 subject in each group. With an inflations factor of 1.5 due to the cluster randomization it will require 26 subjects in each group. For generalizability of the results we wish to include at least 10 construction gangs of 3-5 subjects in each group corresponding to approximately. 40 subjects.

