### Strengths and limitations

A strength of the study is that real life measurements on excessive load will be used and shown as video clips to the workers during workshops as part of a participatory intervention, and thereby not limited to self-reported data and biomechanical laboratory studies. This will likely serve as an engaging, visual contextually relevant tool for both workers and managers, since they will be able to see what they are doing when exposed to excessive loads. Furthermore, the use of technical measurements will provide detailed information about the physical load in the construction industry.

The limitations of the study include the challenge to recruit construction crews performing the same work tasks during the intervention period. Construction work is often of a very varying character compared to other types of production. Due to the fact that construction work often is physically strenuous, the workers can sweat a lot during a working day, resulting in altered EMG recordings. However, we have experience from other studies [27, 28, 55], and will ensure that the electrodes are fastened in the best possible manner, and the reference lifts performed in the morning and the afternoon will provide information of possible changes in the EMG activity.

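### The one random effect stated has, read literally, no gang-level term; unless gang-level terms are named and baseline's role is fixed, intervals for the primary comparison can be too narrow

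*Protocol article*

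**What the plan says.** The Statistics section of the protocol article specifies a "repeated-measures linear mixed model with" group, time and their interaction as fixed effects. The only random effect is given as "Participants nested within gangs will be entered as random effect to account for clustering". On covariates it says: "Analyses will be adjusted for baseline values of the number of events with excessive physical workload, gender and age". On reporting it says: "Outcomes will be reported as between-group least mean square differences with 95 % confidence intervals at follow-up". It does not say whether the baseline measurement is also a row of the outcome vector.

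The Outcomes section defines the endpoint as a change: "The primary outcome of the present study is the change from baseline to follow-up in frequency of events with excessive physical load". Measurements are taken at baseline, 3 months and 6 months (Phase 2 and Effect evaluation sections). About 20 gangs of 3 to 5 workers, some 80 people, are randomised 1:1. The Sample size section allows for clustering: "With an inflations factor of 1.5 due to the cluster randomization it will require 26 subjects in each group".

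**The concern.** The gang is the unit of randomisation, so the uncertainty of the treatment effect depends on how much gangs differ in their change over and above what their individual members would produce by chance. The model must have somewhere to put that variance. A participant(gang) term does not provide this. It links the repeated measurements of one worker and treats two workers in the same gang as unrelated, so it does not do what the sentence says it is for.

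A gang intercept on its own may not be enough either. It is constant over time. If baseline is one of the outcome rows, the intercept drops out of follow-up minus baseline, and a shift that moves the whole gang between measurement days is treated as independent worker-level noise. Such a shift is plausible here, because measurements are made on whatever job the gang has that day. The Strengths and limitations section lists recruiting crews that keep the same tasks as a challenge and notes that "Construction work is often of a very varying character compared to other types of production".

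The consequence would be confidence intervals that are too short and p-values that are too small for the primary comparison.

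**Working it through.** **Inputs.** From the Sample size section: difference 20%, SD about 20%, type I risk 5%, power 80%, inflation factor 1.5. From Study design and Study population: gangs of 3 to 5 (m = 4 used), 20 gangs, 1:1. Assumed: two-sided testing. Not in the article: any intra-gang correlation (ICC), in particular one for change.

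**The plan's own figure.** The normal approximation gives 2 × (1.96 + 0.84)² × (20/20)² ≈ 15.7, so 16 per group. The exact t calculation needs 17 (power 0.807, against 0.781 at 16). Then 17 × 1.5 = 25.5, rounded up to 26. The stated 17 and 26 reproduce.

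**ICC implied by the inflation factor.** Design effect D = 1 + (m − 1) × ICC, so ICC = 0.5/(m − 1): 0.25, 0.167 and 0.125 for gangs of 3, 4 and 5.

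**What each reading leaves out.** Write the outcome of a worker at a visit as fixed part + gang intercept + worker intercept + gang-by-visit shift + residual.

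- Reading (a), participant(gang) only: neither gang term is modelled.
- Reading (b), gang and participant intercepts with baseline as an outcome row: both intercepts cancel from follow-up minus baseline, and the gang-by-visit shift is left in the residual.
- Reading (c), gang and participant intercepts, 3- and 6-month values only, baseline as covariate: the gang intercept absorbs whatever gang-level change the two follow-ups share.

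**Size under (a) and (b).** If gang-level change is ignored, the standard error is 1/√D of the right size and the type I error is 2 × (1 − Φ(1.96/√D)). At D = 1.5 the ratio is 1/√1.5 = 0.816, about 18% too small. 1.96/√1.5 = 1.600, and 2 × (1 − Φ(1.600)) = 0.1095, about 11%. At D = 1.5 this does not depend on gang size.

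For m = 4, by ICC of change:

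| ICC | D | SE ratio | Type I error |
|---|---|---|---|
| 0.01 | 1.03 | 0.985 | 0.0535 |
| 0.05 | 1.15 | 0.933 | 0.068 |
| 0.10 | 1.30 | 0.877 | 0.086 |
| 0.167 | 1.50 | 0.816 | 0.11 |
| 0.30 | 1.90 | 0.725 | 0.155 |

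**Simulation, all readings.** 20 gangs of 4, three occasions, no treatment effect, change ICC 0.167, 2,500 runs per cell. The two figures are for gang shifts that are the same at both follow-ups and for shifts that are independent between them.

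| Analysis | Same shift | Independent shifts |
|---|---|---|
| (b) intercepts only, baseline an outcome row | 0.126 | 0.108 |
| (a) participant only, baseline-adjusted mean of follow-ups | 0.125 | 0.097 |
| (c) gang intercept, baseline-adjusted mean of follow-ups, t with 17 df | 0.043 | 0.044 |
| (c) same, normal reference | 0.058 | 0.060 |
| t-test on gang means of change | 0.048 | 0.047 |

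**Reading (c) at a single visit.** The runs above average the two follow-ups, so they do not test whether a constant gang intercept suffices for the contrast at one visit. A further simulation did (10,000 runs, change ICC 0.167, within-worker sharing between visits assumed to be 0.5):

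| Gang-level change across visits | t, 18 df | Normal reference |
|---|---|---|
| Fully shared | 0.043 | 0.059 |
| Half shared | 0.053 | 0.068 |
| Fully visit-specific | 0.064 | 0.084 |

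In the same runs the participant-only model stayed at 0.11 and the t-test on gang means at 0.050 to 0.052. The 18 degrees of freedom are 20 gangs minus 2 arms.

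**The case against.** The strongest reply is that the sentence states its purpose, to account for clustering, and that nesting language is ordinary shorthand for a gang effect plus a participant-within-gang effect. The baseline adjustment and the reporting of differences at follow-up then fit reading (c), which shows no material inflation. This stands: the article permits a sound analysis. It does not require one, because it names no separate gang term and leaves baseline's role open while defining the outcome as a change.

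Three stronger inferences should be resisted.

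- A reader might infer that the false-positive risk of this trial will double. The article supports that only under readings (a) or (b), and only if change clusters as strongly as the planning factor. That factor was attached to normalised EMG, not to change in event frequency, and no ICC is given.
- A reader might infer that the analysis will use participant-level degrees of freedom. No method is stated, and a journal protocol may leave that to the SAP. Degrees of freedom matter here only as a condition for reading (c) to hold its level.
- A reader might infer that the limitations text predicts shared gang-level change. It says that the work varies and that task-stable crews are hard to recruit. It does not say that the shift is common to a gang, or how large it is.

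It might also be said that random-effects detail belongs in the SAP. That does not dispose of the point: the article does state the random effect, and following the statement literally gives the wrong standard error.

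**Conclusion.** The concern holds conditionally. As worded, the random-effects sentence allows analyses with quite different error rates, and its literal reading does not account for gang clustering. Under readings (a) and (b), the nominal 5% test of the primary comparison runs at about 11%, with standard errors about 18% too small, on the assumption that the ICC of change matches the inflation factor of 1.5. With the ICC unknown, the error for gangs of four lies between 5.35% (ICC 0.01) and 15.5% (ICC 0.30). Under reading (c) it stays near 5%, provided gang-level change is largely shared by the 3- and 6-month visits and the reference distribution reflects about 20 gangs. If the shifts are wholly visit-specific, it is about 6% with t and 8% with a normal reference.

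That the sentence is inadequate as it stands is firm. The exact size of the inflation is not.

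**What to change.** Replace the random-effects sentence with wording such as: *The outcomes are the 3- and 6-month values, and the baseline value enters as a covariate only. Gang and participant within gang are random effects. Group contrasts use Kenward-Roger degrees of freedom.* If baseline is kept as an outcome row, or if gang-level shifts may differ between visits, add gang-by-visit as a further random effect. The second condition cannot be ruled out when crews change tasks, so it should be decided before the data are unblinded.

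The cost is a sentence or two of text and a few lines of SAS, with no extra data or participants. Confidence intervals will be somewhat wider than under a model without a gang-level term.

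### Event duration is adjusted for the baseline number of events instead of its own baseline: a minor loss of precision that one sentence would remove

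*Protocol article*

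**What the plan says.** All of this is in the protocol article.

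- **Statistics**, on the model: "The change in frequency and duration of events with excessive physical workload will be evaluated using a repeated-measures linear mixed model". Two event measures therefore go through it.
- **Statistics**, on covariates: "Analyses will be adjusted for baseline values of the number of events with excessive physical workload, gender and age". The sentence does not distinguish between the two measures.
- **Statistics**, on clustering and reporting: "Participants nested within gangs will be entered as random effect to account for clustering", and "Outcomes will be reported as between-group least mean square differences with 95 % confidence intervals at follow-up".
- **Outcomes**: "The primary outcome of the present study is the change from baseline to follow-up in frequency of events with excessive physical load". Duration is not listed there as an outcome; it enters only through the Statistics section.
- **Outcomes** and **Data**, on the questionnaires: "Secondary outcomes are those obtained from the questionnaires", and "The workers will fill out a validated questionnaire at baseline and after the intervention period". Baseline scores will therefore exist, but no model or covariate set is stated for them.

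The text does not say whether the baseline measurement is only a covariate or also a response time point in the repeated-measures model.

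**The concern.** The most useful covariate in a before-and-after comparison is usually the baseline value of the outcome itself. The rule as written supplies it for frequency and withholds it for duration. A worker with a few long events and a worker with many short ones can have similar total exposure and very different counts, so the count is an imperfect stand-in for baseline duration.

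This goes beyond a detail left to a fuller plan. The article names the covariate, and for one of its two modelled measures it names another variable's baseline. An analysis plan that copied the sentence would copy the mismatch. With 20 gangs, chance differences between arms at baseline can be appreciable. Whatever part of a duration imbalance the count does not explain stays in the between-group difference and adds to its standard error.

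**Working it through.** **1. The plan's own figure.** Sample size section: reduction 20 %, SD about 20 %, so a standardised effect of 1.0; type I risk 5 % (taken as two-sided), power 80 %. A two-sample t-test solves to 16.7, so 17 per group, with power 80.7 % at 17. Then 17 × 1.5 = 25.5, so 26. Both stated figures reproduce. The calculation takes no credit for baseline adjustment, so the point leaves the sample size unchanged.

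**2. Assumptions.** The document gives no correlations and says that the reliability of the primary outcome is unknown. Let ρ be the correlation of duration with its own baseline (0.4 to 0.7), and c the correlation of baseline count with baseline duration (0.4 to 0.9). Baseline count is taken to relate to follow-up duration only through baseline duration. Variances are in units of the outcome variance, taken as equal at both times.

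**3. Residual variance.**

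- Own-baseline adjustment: 1 − ρ²
- Follow-up as response, adjusted for count: 1 − (ρc)²
- Change as response, adjusted for count: 2(1 − ρ) − ((1 − ρ)c)²

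| Response | Least loss | Greatest loss |
|---|---|---|
| Follow-up | ρ 0.4, c 0.9: 0.870/0.84 = 1.04 | ρ 0.7, c 0.4: 0.922/0.51 = 1.81 |
| Change | ρ 0.7, c 0.9: 0.527/0.51 = 1.03 | ρ 0.4, c 0.4: 1.142/0.84 = 1.36 |

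The ratio is above 1 throughout the range.

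**4. Power, with ρ = 0.5.** Noncentral t, two-sided 5 %, effective n per group = n/1.5. Own-baseline variance is 0.75. Count-adjusted variance is 0.96, 0.91 and 0.84 for c = 0.4, 0.6 and 0.8; at ρ = 0.5 the follow-up and change responses give the same values.

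| n per group, effect | Count, c 0.4 | Count, c 0.6 | Count, c 0.8 | Own baseline |
|---|---|---|---|---|
| 40, 1 SD | 95.5 % | 96.4 % | 97.4 % | 98.5 % |
| 26, 1 SD | 83.0 % | 84.9 % | 87.6 % | 91.0 % |
| 40, 0.75 SD | 78.3 % | 80.4 % | 83.4 % | 87.3 % |

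The first row is the planned recruitment with the planned effect: a gain of about 1 to 3 points. The 26-per-group row is the calculated minimum. The 0.75 SD effect is an illustration and is not in the document.

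**5. Chance imbalance.** At 40 per group and inflation 1.5, the baseline difference between arms has SD √(2 × 1.5/40) = 0.27 outcome SD. With no baseline adjustment and ρ = 0.5, the part carried into the follow-up difference has SD 0.5 × 0.274 = 0.137. After adjustment for count it is 0.137 × √(1 − c²): 0.13, 0.11 and 0.08 for c = 0.4, 0.6 and 0.8. Own-baseline adjustment takes it to about zero.

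**6. Simulation check.** 20 gangs of 4 and an intraclass correlation of 0.167, which inflation 1.5 implies: 0.5/(4 − 1). At ρ = 0.7 and c = 0.7, the share of a duration imbalance carried into the estimate was about 0.70 unadjusted, 0.35 with count as covariate, about 0 with own baseline, and −0.16 for a change score adjusted for count. The standard error was 0.241 with count, 0.200 with own baseline, and 0.208 for the change score adjusted for count.

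**The case against.** The strongest reply is that the text speaks of evaluating the change. On that reading, baseline duration already enters through the response. This has force: at ρ = 0.7 and c = 0.7 the standard error is then 0.208 against 0.200, a 4 % difference. It does not remove the loss, which grows as ρ falls: the variance ratio reaches 1.36 at ρ = 0.4 and c = 0.4. The article also leaves open which reading applies.

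Second, duration is neither the primary outcome nor a listed secondary one. That is true and limits the importance of the point, but the Statistics section still commits to modelling it.

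Three stronger readings are tempting, and the document does not support them.

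- *The imbalance is left uncorrected.* Count and duration are probably correlated, so the count removes part of it. The 0.137 SD figure describes no baseline adjustment at all, which is not what is planned.
- *Every questionnaire outcome is adjusted for the wrong baseline.* The model is stated for event frequency and duration only. An article may leave the models for secondary outcomes to a fuller plan.
- *The result would be biased or the trial underpowered.* Randomisation keeps the estimate unbiased on average, a valid interval already reflects chance imbalance, and at the planned size and effect power is above 95 % with either covariate.

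**Conclusion.** The point holds for duration, as a matter of precision and not of validity. Read literally, the rule adjusts duration for the baseline of another variable, and this is less efficient than own-baseline adjustment at every correlation examined. The primary analysis of frequency is unaffected.

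The size is uncertain because it rests on assumed correlations, on count relating to follow-up duration only through baseline duration, and on whether follow-up or change is the response. The range runs from negligible (variance ratio 1.03) to substantial (1.81), with a small effect on power at the planned recruitment and effect. It matters more for smaller effects and for the width of the interval. This is a minor, free improvement.

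**What to change.** Replace the covariate sentence in the Statistics section with: *Each analysis will be adjusted for the baseline value of the outcome being analysed (number of events for frequency, baseline duration for duration), gender and age.* Apply the same rule to the questionnaire scores if they are analysed with this model. In the same edit, state whether baseline is a covariate or a response time point.

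The cost is a sentence or two, settled before unblinding. The baseline values are already collected, the number of covariates per model is unchanged, and the frequency analysis keeps its present baseline covariate. A worker with no baseline duration needs the same handling as one with no baseline event count; as both come from the same recording, this should seldom add a new case. Fixing the rule now also removes a later choice of covariate for duration.
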